#### Randomization and blinding

2.3.2

Randomization is standardized in this study in combination with the design characteristics of the three parts of the experiment: The first part is a case–control observational study. After screening through strict inclusion and exclusion criteria, the case group (patients with lumbar muscle strain) and the control group (healthy people without lumbocrural pain) are selected from the eligible population by simple random sampling (15 cases in each group) to ensure sample representativeness, with no inter-group random allocation involved. The second part is a cross-over design study, in which 24 patients with lumbar muscle strain are divided into 3 groups (8 cases in each group) by complete randomization, receiving three sequences of rolling manipulation intervention with low-medium-high, medium-high-low and high-low-medium pressure, respectively. The third part is an interventional trial involving 69 participants in total. 46 patients with lumbar muscle strain are stratified by age and disease duration and then divided into a case intervention group (rolling manipulation intervention, *n* = 23) and a case control group (health education intervention, *n* = 23) by the random number table method; additionally, 23 healthy controls are selected by simple random sampling.

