#### Part 3: clinical efficacy and cortical hemodynamic responses with optimal pressure

2.4.3

The experiment is divided into three groups, with healthy individuals without lumbocrural pain serving as the healthy control group, who receive intervention using optimal pressure parameters of the rolling manipulation. The protocol is 3 times per week, with one week as one treatment course, for a total of one course (3 interventions). This intervention is administered to investigate cortical hemodynamic changes induced by rolling manipulation with optimal pressure and to assess neuromuscular responses in healthy individuals with intact lumbar muscles, enabling a direct comparative analysis of brain functional and biomechanical responses to the identical manual intervention between healthy subjects and patients with lumbar muscle strain. fNIRS data are collected immediately before, during and after the 1st and 3rd interventions, while muscle tension and pressure pain threshold data are obtained before and after the intervention. Patients with lumbar muscle strain are divided into two groups: a case control group and a case intervention group. The case control group receives health education, whereas the case intervention group receives optimal-pressure rolling manipulation. The health education mainly covers posture management in daily life and work, lumbar protection, and guidance on appropriate physical activity and exercise, with participants’ questions addressed as needed. For both groups, the intervention protocol is 3 times per week, with one week as one treatment course, for a total of two courses. Muscle tension, pressure pain threshold, the Oswestry Disability Index (ODI) and VAS scores are assessed before intervention and immediately after the 1st, 3rd and 6th interventions, at the same detection positions as in Part 1. For the case intervention group, fNIRS data are additionally collected before, during and after the 1st and 3rd interventions. During fNIRS acquisition, participants remained in a prone position with the head and upper chest supported by soft pillows, and the forearms crossed under the forehead to provide additional head support. This posture ensured that the head remained in a relaxed and stable position. The rolling manipulation was applied exclusively to the lumbar region using a smooth, continuous rolling technique without abrupt flicking or plucking motions, thereby minimizing mechanical transmission to the head. The enrollment schedule and assessment protocol are shown in Table 2.

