Oswestry Disability Index (ODI) (Part 3): The primary clinical outcome is the Oswestry Disability Index (ODI). The main analysis will compare the change in ODI from baseline to immediately after the 6th intervention between the case intervention group and the case control group. We expect a greater reduction in ODI in the case intervention group. ODI will also be assessed after the 1st and 3rd interventions to describe the course of clinical change. It covered 10 dimensions including pain intensity, activities of daily living, walking, sitting and sleeping, with 0–5 points for each dimension. The total score is converted into a percentage (0–100%), with a higher score indicating more severe dysfunction. Data are collected before intervention and immediately after the 1st, 3rd and 6th interventions to evaluate improvements in patients’lumbar function. If no more than 1 item is missing, the value is replaced by the average score of the completed items; if 2 or more items are missing, the data are regarded as invalid.

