### Sample size calculation

2.8

Based on the core research objectives and design types of the three parts, this study is overall planned as follows:

The first part is an observational study, with the fNIRS-derived cortical hemodynamic response (HbO/HbR changes) as the primary outcome. Based on repeated measures analysis of variance (effect size *f* = 0.286, α = 0.05, 1−β = 0.8) (30), G*Power 3.1.9.7 calculation showed that 12 cases are needed in each group. Considering a 20% attrition rate, 15 cases are included in both the healthy control group without lumbocrural pain and the lumbar muscle strain case group, with a total of 30 cases.

The second part is a cross-over design. The sample size was estimated based on the median frequency (MF) of the surface electromyographic (sEMG) signals, one of the primary electromyographic outcomes for screening the optimal pressure. Referring to our previous study on rolling manipulation in patients with lumbar muscle strain (13), the within-individual standard deviation of sEMG frequency was 17.09 Hz and the intraclass correlation coefficient was 0.5. Repeated Measures ANOVA combined with Greenhouse–Geisser corrected F test (α = 0.05, 1-β = 0.8) was adopted. PASS 2021 software calculation showed that 17 cases are needed. Considering a 20% attrition rate, 24 patients with lumbar muscle strain are included and randomly divided into 3 group sequences.

The third part took the change in the Oswestry Disability Index (ODI) from baseline to immediately after the 6th intervention as the primary clinical endpoint for the comparison between the case intervention group and the case control group. Based on a two-independent-sample design, in which the expected between-group difference (μ2 − μ1 = 10) and the standard deviation (σ = 9) were derived from a previous study on massage combined with functional exercise for chronic lumbar muscle strain (31), With α = 0.05 and 1 − β = 0.80, the calculation showed that 18 patients were required in each group. Considering a 20% attrition rate, 23 patients with LMS will be enrolled in the case intervention group and 23 in the case control group, resulting in a total of 46 patients with LMS. In addition, 23 healthy controls will be enrolled as a reference group for the fNIRS and biomechanical comparisons. Therefore, Part 3 will include 69 participants in total, comprising 46 patients with LMS and 23 healthy controls.

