Although this study has significant advantages in research design and technology integration, there are still potential limitations based on the current technological development and research conditions: Restricted by the inherent characteristics of fNIRS technology, it could only detect changes in cerebral cortical blood oxygen concentration and could not explore the functional changes of subcortical pain-related nuclei such as the thalamus and amygdala, which might lead to an incomplete characterization of subcortical pain-related processes (48). The study intended to screen the optimal parameters using low, medium and high force levels, but has not yet conducted an in-depth exploration of the precise force values and pressure distribution within the optimal level, and it is necessary to improve the individualized adjustment scheme of manipulation parameters in the future. The single-center study design results in a relatively high homogeneity of the enrolled population, and even if the sample size is scientifically estimated and the attrition rate is reserved, the extrapolability of the research results may still be affected to a certain extent. The case control group in this study receives health education, with the aim of evaluating the clinical effect of optimal-pressure rolling manipulation relative to health education. The present study does not separately address the effects of treatment time, physical contact, placebo effects, or other nonspecific factors. In addition, the treating practitioner cannot be blinded to the intervention being delivered, which is an inherent limitation of manual therapy trials. This potential performance bias will be mitigated by blinding the outcome assessors and data analysts.

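### The 10-point ODI difference used to size Part 3 comes from a different treatment contrast, and the stated 18 per group does not match the stated 80% power

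*Protocol article*

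**What the plan says.** **Planning inputs (protocol article, section 2.8).** The calculation uses two independent samples, with "the expected between-group difference (μ2 − μ1 = 10) and the standard deviation (σ = 9"). Both values "were derived from a previous study on massage combined with functional exercise for chronic lumbar muscle strain (31"). The result is given as "With α = 0.05 and 1 − β = 0.80, the calculation showed that 18 patients were required in each group", and then "Considering a 20% attrition rate, 23 patients with LMS will be enrolled in the case intervention group and 23 in the case control group". The article does not state whether the test is one- or two-sided. It also does not give the cited study's comparator, dose or duration.

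**Contrast tested.** Section 2.3.2 has patients "divided into a case intervention group (rolling manipulation intervention, *n* = 23) and a case control group (health education intervention, *n* = 23"). Section 2.5.2 sets the primary clinical comparison: "The main analysis will compare the change in ODI from baseline to immediately after the 6th intervention between the case intervention group"; its counterpart is the health education arm. Section 2.4.3 describes no exercise component in the rolling arm. Of the control arm it says: "The health education mainly covers posture management in daily life and work, lumbar protection, and guidance on appropriate physical activity and exercise". The Discussion confirms that the control was chosen "with the aim of evaluating the clinical effect of optimal-pressure rolling manipulation relative to health education".

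The article neither adjusts the 10 points for this difference in treatments nor says why they should carry over.

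**The concern.** A sample size is only as good as the match between the effect assumed and the effect to be estimated. Here the source's active treatment was a package of massage and functional exercise. In Part 3 the exercise component is absent from the active arm, and the control arm receives some exercise-related advice. If exercise contributed to the source's 10 points, or if the advice lowers ODI in controls, the difference to be expected here would be smaller.

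ODI change is the primary clinical endpoint of Part 3, and section 2.8 is the only power justification that the article gives for it. If the true difference were well below 10, a non-significant result could be read as evidence against rolling manipulation when the trial had little chance of detecting the effect. The stated 18 and 80% therefore need to be right, and readers need to know how far the assumption can slip before power is lost.

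**Working it through.** **Inputs.** Difference Δ = 10, SD σ = 9, α = 0.05, power 0.80, 18 per group before attrition, 20% attrition and 23 enrolled per group, all from section 2.8. Allocation is 1:1 (section 2.3.2). Two-sided testing is my assumption.

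**Step 1: reproduce the 18.**

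Normal approximation: n = 2(z₁₋α/₂ + z₁₋β)² σ²/Δ² per group.

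- 80% power: 2 × (1.960 + 0.842)² × 81/100 = 12.7, so 13. The exact t-test solution is 13.75, so **14**.
- One-sided 0.05, 80% power: 11 by either method.
- 90% power, two-sided: 2 × (1.960 + 1.282)² × 81/100 = 17.0, which rounds up to 18. The t-test solution is 18.04.

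The stated 18 is not reproduced at 80% power. It could have arisen in several ways:

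- 90% power was used, two-sided.
- 95% power was used, one-sided.
- The 20% attrition had already been applied: 14/0.8 = 17.5, so 18.
- A larger SD was used: about 10.4 gives 18 at 80%.

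The article does not say which. The last step does reproduce: 18/0.8 = 22.5, so 23.

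**Step 2: power at the stated inputs.** For the two-sample t test the noncentrality is (Δ/σ)√(n/2) with 2n − 2 degrees of freedom. At n = 18 and Δ = 10 it is (10/9) × 3 = 3.33 on 34 degrees of freedom, giving power 0.899 (0.915 by the normal approximation).

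**Step 3: power if the true difference is smaller.** The documents give no effect for rolling against health education, so the range below is an assumption. SD is held at 9, two-sided 0.05, t test.

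| True difference | Power, 18 per group | Gap to stated 80% at 18 | Power, 23 per group |
|---|---|---|---|
| 10 | 90% | none | 96% |
| 9 | 83% | none | 91% |
| 8.65 | 80% | none | – |
| 8 | 74% | 6 points | 84% |
| 7.6 | – | – | 80% |
| 7 | 62% | 18 points | 73% |
| 6 | 49% | 31 points | 60% |
| 5 | 37% | 43 points | 45% |

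The gaps are measured from the 80% that the article claims, not from the 90% that 18 per group actually gives.

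**Step 4: does the unknown comparator matter?** There are three possible forms of the source comparison:

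- Massage plus exercise against exercise gives the add-on effect of massage.
- Massage plus exercise against massage gives the effect of exercise.
- Massage plus exercise against another treatment gives a package effect.

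None of these is rolling without exercise against education with exercise advice. The contrasts differ in every case, but this alone does not fix the direction of the error.

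**The case against.** **The direction is unknown.** If the cited study used an active comparator, its difference need not exceed that of rolling against education. This stands: the documents do not show that 10 is too high, only that it is unsupported for this contrast.

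**The control arm receives advice, not an exercise programme.** This also stands. Section 2.4.3 describes guidance alongside posture and lumbar protection, and nothing in the article shows that it lowers ODI over two weeks. It should not be equated with the functional exercise of the source study.

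**A reader might infer that any true difference below 10 forfeits the stated 80% power.** The figures contradict this. Because 18 per group is more than the inputs require, power is still 83% at 9 points and 80% at 8.65. A reader might go further and conclude that Part 3 is underpowered, but the mismatch does not show that either.

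**Borrowing an effect from a related treatment is common, and a condensed article may leave the reasoning to the full protocol.** This is fair as far as the justification goes, and it keeps that part of the point modest. It does not cover the arithmetic: the article itself prints 18, 10, 9 and 80% together, and they do not agree.

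**Conclusion.** Two things hold. First, the 10-point difference and SD 9 come from a treatment package that Part 3 does not test, and the article offers no reason for carrying them over. They are a planning assumption whose error, if any, has unknown direction and size. Second, the stated set of figures is wrong as written: 14 per group suffices for 80% power at those inputs, and 18 gives about 90%.

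The second fact softens the first. At SD 9 and two-sided 0.05, the claimed 80% survives with 18 evaluable per group unless the true difference is below 8.65 points, or below 7.6 points if all 23 are retained. Beyond that the loss is substantial: at 18 per group, about 6 percentage points below the stated 80% at a difference of 8, and 18 at a difference of 7. These losses are conditional on assumed differences and on SD 9, which comes from the same source. For scale, at 10 points an SD of 12 would give 68% power with 18 per group.

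**What to change.** Revise the Part 3 paragraph of section 2.8, leaving enrolment at 23 per group:

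1. State that the 10 points and SD 9 come from a study of a different contrast. Then either justify them for rolling against health education or label them as an assumption.
2. Reconcile the 18 with the stated 80%. Give the sidedness and say whether 18 reflects 90% power, attrition already applied, a different SD or something else. If attrition is already in the 18, the step to 23 applies it twice, and the text should say so.
3. Restate power as a detectable difference. For example: *with 18 evaluable patients per group, SD 9 and a two-sided 0.05 t test, Part 3 has 80% power for 8.65 ODI points, 90% at 10, 74% at 8, 62% at 7 and 37% at 5; with all 23 retained, 80% power is reached at 7.6 points.*

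Step 2 has to accompany step 3. Otherwise the paragraph would give 18 per group as both the number required for 80% power at 10 points and the number giving 80% at 8.65.

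The cost is rewording. No arm, endpoint, visit or number enrolled changes. The authors would be showing openly that power falls below 80% if the true difference is under 8.65 points.

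### The Part 3 sample size does not follow from its printed inputs: a difference of 10, SD 9, alpha 0.05 and 80% power need 14 patients per group, not 18

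*Protocol article*

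**What the plan says.** Section 2.8 (Sample size calculation) of the protocol article sizes Part 3 on the comparison of the case intervention group with the case control group:

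- Endpoint: "The third part took the change in the Oswestry Disability Index (ODI) from baseline to immediately after the 6th intervention as the primary clinical endpoint".
- Comparison: "Based on a two-independent-sample design".
- Effect and spread, both attributed to one earlier study: "the expected between-group difference (μ2 − μ1 = 10") and "the standard deviation (σ = 9").
- Error rates: "With α = 0.05 and 1 − β = 0.80".
- Result: "the calculation showed that 18 patients were required in each group".
- Enrolment: "Considering a 20% attrition rate, 23 patients with LMS will be enrolled in the case intervention group and 23 in the case control group".

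For Part 3 the section gives no sidedness, software or formula, although it names the software for Parts 1 and 2. It mentions no alpha adjustment, no allowance for a rank test and no other factor that would raise the number. Section 2.5.2 confirms that the main ODI analysis is this single between-group comparison of change to the sixth intervention.

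**The concern.** The sentence prints every input that a two-sample calculation for means needs, apart from sidedness, and it also prints the answer. A standardised difference of 10/9, about 1.1, is large, and 18 per group is noticeably more than 80% power requires for it.

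This calculation is the only stated basis for randomising 46 patients on the primary clinical endpoint. If the inputs and the number disagree, at least one printed figure is wrong or a step has been left out. A reader then cannot tell which power, SD or difference the trial was planned on, and anyone reusing the figures to plan a later trial may carry the error forward.

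**Working it through.** **Inputs (section 2.8):** difference δ = 10, SD σ = 9, alpha = 0.05, power = 0.80, equal allocation, attrition 20%. Sidedness is not stated. Two-sided is assumed, and one-sided is shown as well.

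**1. The plan's own figures.** The attrition step reproduces: 18/(1 − 0.20) = 22.5, rounded up to 23. The 18 itself does not reproduce from the printed inputs, as steps 2 and 3 show.

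**2. Normal approximation.** n per group = 2(z₁ + z₂)²σ²/δ², with 2σ²/δ² = 2 × 81/100 = 1.62.

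- Two-sided, 80% power: 1.62 × (1.960 + 0.842)² = 12.7, so 13.
- One-sided, 80% power: 1.62 × (1.645 + 0.842)² = 10.02, so 11.
- Two-sided, 90% power: 1.62 × (1.960 + 1.282)² = 17.03, so 18.

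**3. Exact two-sample t test.** Power comes from the noncentral t distribution with 2n − 2 degrees of freedom and noncentrality δ/(σ√(2/n)). For n = 18 the noncentrality is 10/(9 × √(1/9)) = 3.33. Two-sided results at alpha 0.05:

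| n per group | power |
|---|---|
| 13 | 0.776 |
| 14 | 0.808 |
| 18 | 0.899 |
| 23 | 0.958 |

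So 80% power needs 14 per group and 90% power needs 19. A one-sided t test at 80% power needs 11.

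**4. Size of the gap.** With 14 evaluable per group, 20% attrition gives 14/0.8 = 17.5, so 18 enrolled per group and 36 in all. The plan enrols 23 per group and 46 in all.

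**5. Routes that would lead to 18.**

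- *Power of about 90%.* The normal approximation gives exactly 18. The t test just misses, with 0.899 at 18.
- *Attrition applied twice.* 14/0.8 = 17.5, rounded up to 18. Then 18/0.8 = 22.5, rounded up to 23. This keeps every printed input, including the 80% power.
- *A different SD or difference.* By t test, 18 per group give 80% power at a standardised difference of 0.961. That means an SD of about 10/0.961 = 10.4 with difference 10, or a difference of about 0.961 × 9 = 8.65 with SD 9. Neither value is printed.

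**6. Adjustments that do not rescue the sentence as printed.** Allowing for a rank test gives at most 14/0.864 = 16.2, so 17. An alpha of 0.025 gives 16 (normal) or 17 (t), and 0.0167 gives 17 or 19. The section states 0.05 and mentions no rank-test allowance.

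**The case against.** The best counter-argument is that the discrepancy is harmless. It errs in the safe direction: power on the printed inputs exceeds the stated 80% at both 18 and 23 per group. Enrolment, endpoint, allocation and analysis are untouched, and the eventual ODI result will be read from its estimate and interval rather than from planning figures. All of that stands, and it limits the weight of the point. It does not make the sentence correct.

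A second objection is that a journal article condenses the full protocol, so an unstated factor might explain the 18. Missing sidedness or software would indeed be no finding. Here, however, the inputs and the result are both printed and they disagree. Leaving the sidedness open does not help, because a one-sided test moves the requirement further away, to 11.

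A reader might infer that the trial was really designed for 90% power. The documents do not support that. The match at 18 is exact only by the normal approximation, under which the 80% figure is 13. By the t test that gives 14, 90% needs 19. Double counting of attrition fits the printed inputs equally well. A reader might equally take double counting as established, or suppose that 9 is the SD of a single score and a larger SD of the change was used. Nothing in the article shows either.

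**Conclusion.** The figure of 18 per group is wrong as written for the inputs printed beside it. The requirement at 80% power is 14 per group by two-sided t test. This rests on reading the inputs as the article gives them, with a standard two-sample comparison of means and equal allocation. The two-sided choice favours the plan.

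The overstatement is 4 evaluable patients per group (18 − 14), or 5 enrolled per group (23 − 18). The documents cannot settle whether the power, the attrition step, the SD or the difference is at fault, so the point is a failure to reconcile and not a diagnosis. It is no ground for calling Part 3 underpowered. It is worth correcting because the sentence justifies the size of the randomised comparison and the correction is easy.

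**What to change.** Keep 23 patients per group. Recheck the Part 3 calculation against its source output and rewrite the sentence in section 2.8 so that the difference, SD, alpha with its sidedness, power and number agree.

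- If a difference of 10 and an SD of 9 are the real inputs, state that 14 evaluable patients per group are required for 80% power (two-sided t test), and that the 18 evaluable per group expected after 20% attrition give about 90%.
- If another SD or difference was used, print that value in place of the present one.

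The 90% should not be presented as the original design target unless the sponsor confirms that it was. The cost is one sentence and a rerun of a short calculation, with no change to enrolment, endpoint or analysis.
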